## Abstract

**Background:**

Attention deficit hyperactivity disorder (ADHD) is one of the most common mental disorders observed in childhood and adolescence. Its key symptoms — reduced attention, poor control of impulses as well as increased motor activity — are associated with decreased executive functions performance, finally affecting academic achievement. Although drug treatments usually show some effect, alternative treatments are continually being sought, due to lack of commitment and possible side effects. Cognitive trainings are frequently used with the objectives of increasing executive function performance. However, since transfer effects are limited and novelty and diversity are frequently ignored, interventions combining physical and cognitive demands targeting a broader range of cognitive processes are demanded.

**Methods:**

The aim of the study is to examine the effects of a cognitively and physically demanding exergame on executive functions of children with ADHD. In a randomised clinical trial, 66 girls and boys diagnosed with ADHD (age 8–12) will be assigned either to an 8-week exergame intervention group (three training sessions per week à 30 min) or a waiting-list control group. Before and afterwards, the executive function performance (computer-based tests), the sport motor performance and ADHD symptoms will be assessed.

**Discussion:**

The current study will offer insights into the effectiveness of a combination of cognitive and physical training using exergaming. Positive effects on the executive functions, sport motor performance and ADHD symptoms are hypothesized. Beneficial effects would mean a large degree of scalability (simple and cost-effective) and high utility for patients with ADHD.

**Trial registration:**

KEK BE 393/15 (March 8, 2016); DRKS00010171 (March 14, 2016)

## Background

Children and adolescents with attention deficit hyperactivity disorder (ADHD) display an increased risk of suffering from long-term academic, work-related and social impairments, which are linked to the key symptoms of ADHD: impaired attention, hyperactivity and lack of control of impulses [1]. ADHD is one of the most common disorders in childhood and adolescence with an estimated prevalence of 3–7% [2, 3], affecting more boys than girls [4]. The key symptoms usually already occur at pre-school age and may persist into adulthood [5]. Neurocognitive consequences of the disorder may take the form of deficient executive functions and motor deficiencies [6–8].

Although a large proportion of the symptoms can be reduced by medication, the main method of treatment [9], medications are also associated with a series of difficulties. Not all patients respond to treatment, about one third does not respond or responds poorly to treatment [10–12]. In some cases, side effects [13], low compliance [14] and as yet largely unknown long-term sequelae [15] occur. For these reasons, alternative methods of treatment are constantly being sought, which can improve the main functional deficits associated with the symptoms of ADHD. The prevailing explanation for the development of the key symptoms of ADHD is seen in a primary deficit in the executive functions [16].

Pronounced ADHD symptoms (attention deficit, hyperactivity, impulsiveness) are negatively correlated with the executive function performance [17–22]. Executive functions are viewed as meta-cognitions which are necessary for the top-down modulation of fundamental cognitive processes and therefore for carrying out goal-oriented activities [23]. Three fundamental processes can be seen as forming the core of the executive functions: *inhibition*, *working memory* and *cognitive flexibility* [24]. The executive functions are involved in all patterns of goal-oriented thought and behaviour and therefore control all behaviour that is relevant to learning [23], which explains the strong connection between learning success and executive functions in children in general [25] as well as in children with ADHD [26]. Promoting executive functions could therefore be a key pillar in a successful treatment strategy aiming to reduce the key symptoms of ADHD.

The positive influence of increased physical exercise on a wide range of areas of cognition has been repeatedly demonstrated for all age groups [27, 28]. In particular, inhibition and cognitive flexibility seem to profit from it [29]. Since children with ADHD often display deficient motor skills and motor control in addition to a functional deficit in their executive functions [30], increased physical exercise might be particularly important to this study population. Promising effects of physical activity, mostly based on acute studies, have been demonstrated in children with ADHD [31], and these might be explained by a potentially strong link between sensory motor skills, higher order cognitive processes and academic achievement [32]. Aside from these cross-sectional studies, experimental studies aiming to examine the longer-term influence of physical exercise on cognitive performance in childhood are rare [33] and even more so for children with ADHD [34].

The few existing intervention studies mostly reveal positive effects on cognitive performance [35–41], whereby multimodal treatment methods in particular are attributed with a greater efficacy and broader transfer effects (also to health and well-being). In this context, qualitative characteristics of the physical activity, such as adaptiveness to the individual performance level and cognitive demands, are attributed with playing a central role [42]. The fact that a training programme needs to be individually customised and adaptive in order to have positive effects on the executive functions is generally accepted in the field of cognitive training [43, 44].

The effectiveness of cognitive training programmes has increasingly been studied in children with ADHD in recent years [45]. This was mostly done using computerised, adaptive training programmes, aiming at attention processes, working memory or inhibition, for example. Neuropsychological deficits are to be reduced and transfer effects to the symptoms of ADHD and the general level of functioning are to be facilitated [46]. However, such effects seem to be limited to improvements in working memory performance [45]. Since most training programmes only aim at one area of the executive functions (e.g. working memory) [47], the transfer effects to other fundamental processes and to the ADHD symptoms as a whole continue to be a matter of controversy [48]. Thus, for example, improved working memory only leads to an improved learning performance if the child is able to block out (inhibit) irrelevant information. Cortese et al. [45] therefore call for innovative treatment programmes that increase transfer effects and that target multiple neuropsychological processes.

Just as there have been promising developments towards making cognitive training programmes as multifaceted as possible, the idea that highly varied, cognitively demanding sports activities offer an additional benefit for the executive functions [49] is increasingly being pursued in the field of physical training programmes too [23, 50]. A recent study [51] was able to demonstrate that a 6-week, cognitively demanding sports game intervention, but not a pure aerobic exercise intervention, had a positive influence on the cognitive flexibility of primary school children. In order to have the largest possible effect, Moreau and Conway [52] recommend a combined physical and cognitive training programme. This should ideally be carried out in the form of an ecologically valid but nevertheless controllable study.

An innovative combination of physical and cognitive training that takes into account the recommendations of Moreau and Conway [52] can be achieved with the help of “exergaming”. Exergaming is a portmanteau of “exercise” and “gaming” and refers to a new genre of interactive video games, which allow the gaming experience to be extended to the entire body [53]. In the light of existing motivational problems and a lower level of positive reinforcement, children with ADHD often find conventional training programmes boring and tiring [47]. “Gamification”, on the other hand, i.e. the use of game elements in non-game contexts [54, 55], appears to have a positive effect on motivation and training outcomes [56, 57]. This connection leads to a hybrid form that lies between a physical and cognitive training programme and a video game. This form of training ensures adaptivity. The duration, intensity, complexity and quality of execution of the physical training can be measured. No studies currently exist on exergames and their effects on the cognitive skills of children with ADHD. However, initial investigations with children and adolescents have yielded promising results and therefore seem to demonstrate the usefulness of exergames as an intervention for promoting health-related outcomes [58] and the executive functions [59–62].

### Study aims and hypotheses

The aim of this study is to evaluate the influence of an exergame intervention, which is characterised by both high physical and high cognitive demands, on the executive functions of children with ADHD. We expect that exergaming will have a positive impact on the executive functions, the sport motor performance, the symptoms of ADHD and on quality of life.

As the primary outcome, we hypothesize that exergaming will positively affect executive function performance compared to controls. More specifically, we expect that the demanding exergame activity that will be carried out over a period of 8 weeks will have a beneficial effect on the key areas—inhibition, working memory and cognitive flexibility—and that we will be able to detect a significant effect (significance level α = .05) with small to moderate effect sizes.

As secondary outcomes, we hypothesize that sport motor performance will be significantly improved by the planned intervention (physically strenuous exergaming). As a further secondary outcome, the influence of the intervention on the symptoms of ADHD will be examined. Based on studies into physical training programmes for children and adolescents with ADHD [42], we hypothesize the intervention to have a positive effect. In addition, quality of life is to be measured as a further secondary outcome serving as an indication of a broad transfer. We expect exergaming to have a positive influence on quality of life. The expectations of registering positive developments with respect to the secondary outcomes are generally somewhat more conservative. Based on the available empirical evidence, we therefore expect to obtain small effect sizes.

## Methods/Design

### Study design

The present study will be carried out using a randomised study design with a waiting-list control group in Bern, Switzerland. Each participant in the study will take part in the study for a total of nine weeks, being assigned either to the exergame intervention or to the passive waiting-list control group.

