### Participants

In total, 66 children with ADHD between the ages of 8 and 12 years should be examined. Any child that has been diagnosed with the ADHD is eligible to take part in the study. Beyond this, the participants and legal guardians must examine the information relating to the study and give their informed consent to take part in the study. As the well-being of the participants is the main priority, people whose mental or physical integrity might be threatened by the study must not take part in it. For safety reasons, people suffering from a neurological disorder, Tourette syndrome or an epileptic disorder will not be allowed to take part. To recruit the study participants, we will collaborate with elpos Schweiz (an association for parents and caregivers of children and adults with ADHD). The sample size of 66 participants was calculated using G*Power [63] for a general linear model with repeated measures (two comparison groups; three measurements; “within-between interaction”; correlation between measurements = .8), with a power of .80 [64] and a small effect size.

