### Outcome measures and time-points of assessment

The study is divided up into five phases (T1-T5). These are discussed in chronological order below (see Fig. 1):Baseline (T1): At the beginning of the study, the participants will be fitted with an accelerometer (Actigraph GT9X), which they are expected to wear during the entire study, to monitor their *physical activity level*. By measuring the acceleration in three-dimensional space, it is for example possible to calculate step counts and MET levels. Participants will be asked to wear the devices at night too, if possible, to obtain data on sleep duration.Pre-intervention measurement (T2): The executive functions, sport motor performance, ADHD symptoms, quality of life and background variables will be measured 7 days after handing over the accelerometer. The measures used to determine the *executive functions:* working memory, cognitive flexibility and inhibition, are based on three standardised tests. They are specifically designed for the age group in question and have proven their age adequacy and sensitivity to changes in executive function performance in previous studies [e.g. 51, 65]: working memory performance will be measured using the colour span backwards [66], in which the number of correct answers will be rated. Cognitive flexibility and inhibition will be measured using the adapted Flanker Test [65, 67, 68], again by computer-assisted means. In this, the scores for accuracy and reaction time will be determined. In addition, an adapted version of the Simon Task [69] will be used. The tests have already been successfully used in several studies [51, 65, 70] and proved to be sensitive enough to detect both acute and chronic effects in children between the ages of 8 and 12 years. The cognitive test battery will last approx. 20 min overall. *Sport motor performance* will be measured using the German Motor Test Battery 6–18, which includes eight test items measuring endurance and coordination [71]. Beyond this, the German version of the Physical Activity Enjoyment Scale will be used to measure the subjective pleasure in physical activity [72]. The Shuttle-run Test [73] will be used to measure physical fitness. The *ADHD symptoms* will be ascertained using the German version [74] of the Conners-3 Scales on Attention and Behaviour [75]. These will be completed by parents and teachers. *Quality of life* will be measured using the Inventory of Quality of Life in Children and Adolescents [76]. This questionnaire will be completed by parents and teachers. The *background variables* will be determined using questionnaires and will include the following: age, sex, height, weight, socioeconomic status [77], exercise behaviour [78], and pubertal development [79], completed by the parents.Intervention phase (T3): The children in the experimental group will train three times a week for approx. 30 min over a period of 8 weeks. The frequency of training and the accuracy will be recorded by the XBOX Kinect and using a Training Diary. In addition, the exercise activity will be recorded by an accelerometer (over a period of 8 weeks) and the heart rate will be recorded by a cardio belt (only during intervention sessions).Post-intervention measurement (T4) and follow-up (T5)*:* At these two times (immediately after the conclusion of the study, and again four weeks later) the tests and questionnaires on the executive functions, quality of life, sport motor performance, attention and behaviour used at T2 will be performed once again.

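### The stated nine weeks end at T4, yet the sample size counts T5 about four weeks later, and the sized interaction test does not isolate the 8-week benefit

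*Protocol article*

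**What the plan says.** All references are to the protocol article.

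- **Study design:** "Each participant in the study will take part in the study for a total of nine weeks". The comparator is a passive waiting list.
- **Outcome measures and time-points of assessment:** the T2 outcomes "will be measured 7 days after handing over the accelerometer". The experimental group then "will train three times a week for approx. 30 min over a period of 8 weeks". T4 and T5 take place "immediately after the conclusion of the study, and again four weeks later". At both, the tests and questionnaires "used at T2 will be performed once again", including the executive function tests, which are the primary outcome.
- **Participants:** the 66 children come from a repeated-measures calculation with "two comparison groups; three measurements", the effect tested being the "within-between interaction", correlation .8, power .80 and an effect size described only as small.
- **Study aims and hypotheses:** the benefit is expected from "the demanding exergame activity that will be carried out over a period of 8 weeks".
- **Data analysis:** repeated measures ANOVA if the groups do not differ significantly before the intervention. Otherwise an ANCOVA takes the post-intervention score as outcome and the pre-intervention score as covariate.

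**The concern.** The stated length of participation and the visit schedule cannot both be right, and the sample size depends on the visit that lies outside the stated length. If T5 is part of the trial, the duration given in Study design is too short by four weeks, and what families are told must match the visits. If nine weeks is right, the calculation behind 66 uses a measurement that will not exist.

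The second issue is what a significant result would mean. The hypothesis concerns the effect of 8 weeks of exergaming, which is read most directly at T4. The interaction over three visits asks whether the group difference changes anywhere among T2, T4 and T5. It can be significant because the groups part only after training has ended. It also draws on T5, where the state of the control group is not described.

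**Working it through.** **1. Timeline.** T1 to T2 is 7 days, or 1 week, and training lasts 8 weeks. T4 falls at 1 + 8 = 9 weeks and T5 at 1 + 8 + 4 = 13 weeks. The abstract mentions testing only before and afterwards.

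**2. Which three measurements.** The executive functions are tested at T2, T4 and T5 and at no other time, so the third measurement is T5.

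**3. Reproducing the 66.** For the within-between interaction with k = 2 groups and m = 3 measurements:

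- λ = f²·N·m/(1 − ρ), df₁ = (k − 1)(m − 1) = 2, df₂ = (N − k)(m − 1)
- From the article: ρ = .8, α = .05, power .80. Assumed: f = .10 for a small effect, sphericity.
- N = 66: λ = 0.01 × 66 × 3/0.2 = 9.9, df 2 and 128, power .8015. N = 65 gives .795, so 66 is the minimum.
- Other values of f at m = 3 do not give 66: f = .125 gives 44 with equal arms, and f = .15 gives 32.

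The figure is therefore exact for three visits under f = .10.

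**4. What the 2-df test responds to.** With group differences δ (in SD) at T2, T4, T5 and equal arms, λ = (N/4)·Σ(δₜ − mean δ)²/(1 − ρ). When λ = 9.9, a difference d sustained at both later visits is d = 0.424.

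| Difference at T2, T4, T5 | Σ(δₜ − mean)² | λ | Power, N = 66 |
|---|---|---|---|
| 0, d, d (sustained) | 0.12 | 9.9 | .80 |
| 0, d, 0 (T4 only) | 0.12 | 9.9 | .80 |
| 0, 0, d (T5 only) | 0.12 | 9.9 | .80 |
| 0, d, d/2 (half left at T5) | 0.09 | 7.4 | .67 |

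The first three rows cannot be told apart by the test. The last row is the least favourable value of T5 for a given T4 difference.

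**5. The direct contrast.** For the T4 difference adjusted for T2 with 66 children, λ = (66/4)·d²/(1 − ρ²), df 1 and 63. For d = 0.424 and ρ = .8: 16.5 × 0.18/0.36 = 8.25.

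| d | ρ = .8 | ρ = .7 |
|---|---|---|
| 0.424 SD | .81 | .66 |
| 0.40 SD | .76 | .61 |

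For comparison at N = 66:

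- T2-to-T4 interaction, d = 0.424, ρ = .8: λ = 16.5 × 0.09/0.2 = 7.4, df 1 and 64, power .765.
- Sized 2-df test, sustained d = 0.424, ρ = .7: λ = 16.5 × 0.12/0.3 = 6.6, power .62.
- Sized 2-df test, sustained d = 0.40, ρ = .8: λ = 16.5 × 0.1067/0.2 = 8.8, power .75.

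The ANCOVA is at least as powerful as the sized test in each of these settings.

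**The case against.** **The nine weeks may be loose wording.** The outcome section puts T4 just after the end of the study and labels T5 a follow-up, so the word study may simply mean the period up to T4. T5 is clearly planned. This stands in part. It makes the duration a short correction, and it means that a trial with only T2 and T4 is not what the article intends. That two-visit case (power .72 at 66 children, 82 needed with equal arms, at f = .10) should not be read as the trial's real power. It also corresponds to 0.40 SD, not 0.424 SD, so it cannot be set against the ANCOVA's .81.

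**Contamination at T5.** A reader might infer that controls have had up to four weeks of the game by T5. The documents do not support that. No passage says when controls receive it, the figure that might show it is not available, and a condensed article may leave it to the full protocol. It remains a possibility.

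**Loss of power.** A reader might also infer that contamination or fading must weaken the sized test. It need not. Power is .67 if half the difference remains at T5, but .80 if all or none of it remains.

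**Choice of test.** An interaction over pre, post and follow-up is conventional, and the hypothesis can be read as a general benefit against controls, with 8 weeks describing only the activity. That is fair, and follow-up contrasts are often left to an analysis plan. It does not remove the ambiguity: a significant interaction alone would not show a benefit at the end of training.

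**Conclusion.** The point holds in a limited form. The stated duration ends at T4, the visit schedule runs to about week 13, and the sample size needs the later visit, so these sections must be reconciled. The figure of 66 is not miscalculated. The 2-df interaction does not isolate the effect of the 8-week activity: a difference of 0.424 SD at T5 alone is as likely to be declared significant (.80) as the same difference at T4 alone.

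The power figures assume f = .10 (the article gives no number), 33 children per arm, complete data, sphericity for the 2-df test and ρ = .8 unless stated. They are sensitive to ρ, as the ANCOVA table shows. Whether the T5 comparison is clean is unknown from the text. This is a clarification plus an improvement at no cost, not a flaw that invalidates the trial.

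**What to change.** 1. **Study design and outcome section:** give one duration that agrees with the visits (13 weeks if T5 is kept) and match it in the family information. State whether the waiting-list group is still untreated at T5.
2. **Data analysis:** make the T4 group difference adjusted for the T2 score the primary analysis. This is the ANCOVA already described there, used whatever a baseline significance test shows.
3. **T5:** compare the groups as a secondary analysis only if controls are still untreated then. Otherwise report T5 descriptively, as within-group follow-up.
4. **Sample size:** restate the power for the T4 contrast with the effect in SD units and the correlation labelled as assumptions, and show the range (.81 and .76 for 0.424 and 0.40 SD at ρ = .8; .66 and .61 at ρ = .7).

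The cost is wording in three sections and in the family information. All the data are already planned, and no more children are needed than for the present test.

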### Participants

In total, 66 children with ADHD between the ages of 8 and 12 years should be examined. Any child that has been diagnosed with the ADHD is eligible to take part in the study. Beyond this, the participants and legal guardians must examine the information relating to the study and give their informed consent to take part in the study. As the well-being of the participants is the main priority, people whose mental or physical integrity might be threatened by the study must not take part in it. For safety reasons, people suffering from a neurological disorder, Tourette syndrome or an epileptic disorder will not be allowed to take part. To recruit the study participants, we will collaborate with elpos Schweiz (an association for parents and caregivers of children and adults with ADHD). The sample size of 66 participants was calculated using G*Power [63] for a general linear model with repeated measures (two comparison groups; three measurements; “within-between interaction”; correlation between measurements = .8), with a power of .80 [64] and a small effect size.

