### Data analysis

The data collected (background variables, primary and secondary outcomes) will be tested as to their statistical properties and analysed accordingly. Normally distributed background and control variables will be compared between the groups (experimental vs. control group) using the two-sample *t*-test, and non-normally-distributed variables will be tested using a Wilcoxon rank-sum test. A chi-squared test will be used for the categorical variables. Significant differences might be considered as covariates for further analyses.

The diary entries as well as the execution data obtained from the XBOX and the heart rate during training sessions will be used to provide information about the focus and the frequency of the training as well as about the level of physical exertion during exergaming. These scores will be presented as descriptive summaries. The frequency of exercises (including step count, MET level) during the intervention period will then be compared between the groups and analysed using an independent *t*-test.

In order to test the hypotheses, the primary and secondary outcome variables will be analysed using repeated measures ANOVAs, if applicable. To determine whether a repeated measures ANOVA is applicable, the pre-intervention scores will be tested using an independent *t*-test to determine any differences between groups. Provided no significant differences are found, the repeated measures ANOVAs can be performed. If, on the other hand, significant differences are found, an ANCOVA should be carried out on the baseline data to check the differences. In this case, the pre-intervention scores will serve as covariates, and the post-intervention scores will be introduced as dependent variables.

The significance level will be set at *p* < .05 for all analyses. The results will be reported in accordance with the CONSORT guidelines for clinical trials [80].

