### Research ethics

The submitted research project has been approved by the ethics committee of the canton of Bern, Switzerland (KEK-NR. 393/15). In addition, the research project has been registered with the Swiss National Clinical Trial Port and the German Register of Clinical Trials (DRKS00010171). After verifying that they are eligible for the study, the participants and their parents will receive adequate verbal information about the study. They will be given enough time to consider their participation and the informed consent information will be sent to them. After at least another seven days, the researcher will visit the families and they will go through the written consent form together. Children above the age of 11 years will be appropriately informed in writing in addition to the oral information. Participation in the study can be terminated at any time without stating the reasons and without detriment to the participant.

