From the point of view of society as a whole, fewer and fewer people are engaging in sports and more and more are failing to meet the recommended daily time spent in physical activity [83]. Physical activity is decreasing and many activities are done seated [84]. At the same time, the amount of time spent in front of screens is becoming longer and longer [81], leading to a link between media use, body fatness and physical activity in children and adolescents [85] and reflecting the particular vulnerability of this study population. In addition, particularly children with ADHD have problems taking part in traditional sports programmes and not dropping out of these [86], which can have negative consequences in many areas, because physical inactivity in children and adults has many effects that are detrimental to health and can be seen as a major health factor [87]. New methods are therefore needed to place the focus on health promotion through sports, and in particularly to encourage children and adolescents who are overtaxed by traditional programmes.

A few limitations need to be mentioned, which might affect the results of the study. First of all, a waiting-list control group is planned, ensuring an economic procedure in view of the low level of available empirical evidence. Should the results be favourable, an exergame intervention would have to be compared with a cognitive training and with a regular physical training programme. The planned exergame intervention is a physical training programme with a high cognitive component. The product in question is commercially available so that the entertainment factor is large and the graphics are appealing. Unfortunately, the exergame was not produced and adapted for the specific use in the current study. As a consequence, the cognitive engagement is greater in some of the game’s levels and lower in others. The cognitive engagement of a cognitive training and an optimal challenge point might not be reached all the time.

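### The 66 children assigned equal the bare complete-data requirement, so power of .80 has no allowance for loss, and classical repeated-measures ANOVA discards any child with a missed visit

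*Protocol article*

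**What the plan says.** The Participants section sets the target: "In total, 66 children with ADHD between the ages of 8 and 12 years should be examined". It gives the source of the number in the same place: "The sample size of 66 participants was calculated using G*Power [63] for a general linear model with repeated measures". The inputs listed are "two comparison groups; three measurements", a within-between interaction, "correlation between measurements = .8", power .80 and an effect described only as small. No dropout rate and no inflation step appear.

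The abstract's Methods paragraph shows that this is also the number allocated: "66 girls and boys diagnosed with ADHD (age 8–12) will be assigned either to an 8-week exergame intervention group".

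The Data analysis section states that "the primary and secondary outcome variables will be analysed using repeated measures ANOVAs, if applicable". ANCOVA of the post-intervention score on the pre-intervention score replaces it only if the groups differ significantly at baseline. Executive functions are tested at T2, T4 and T5, with T5 four weeks after T4 (Outcome measures and time-points of assessment). Under Research ethics, "Participation in the study can be terminated at any time without stating the reasons".

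**The concern.** A power calculation of this type counts children with a score at every measurement. If its output is also the number allocated, each child with incomplete data takes the trial below its planned power. The choice of analysis adds to this. Classical repeated-measures ANOVA needs a full row for each child, so missing the four-week follow-up removes the child's T2 and T4 scores as well, although both were observed.

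Two things are at stake. The first is power: the design starts at .80 with nothing in reserve. The second is bias: only the exergame arm has three home sessions a week for eight weeks, so the reasons for missing a visit could plausibly differ between arms. If they also relate to outcome, a comparison of complete cases would not estimate the effect in all children randomised.

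**Working it through.** **Inputs**

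- From the article: N = 66; groups k = 2; measurements m = 3; correlation ρ = .8; target power .80 (Participants); α = .05 (Study aims and hypotheses; Data analysis).
- Assumed: Cohen's f = .10 for the small effect; nonsphericity ε = 1. The article states neither.

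**Formula (G*Power, within-between interaction)**

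- λ = f² · N · m / (1 − ρ) = .01 · N · 3 / .2 = .15N
- df1 = (k − 1)(m − 1) = 2
- df2 = (N − k)(m − 1) = 2(N − 2)
- Power = P(noncentral F with df1, df2, λ exceeds the central 95% point)

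**Step 1: reproduce the plan's figure**

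| N | λ | df2 | Power |
|---|---|---|---|
| 64 | 9.60 | 124 | .788 |
| 65 | 9.75 | 126 | .795 |
| 66 | 9.90 | 128 | .802 |

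So 66 is the smallest N that reaches .80. The other readings tried do not give 66. With f = .10, two measurements need 82, four need 56 and five need 50 (even totals); with three measurements, f = .15 needs 32. The agreement supports f = .10 and ε = 1 as the inputs used, and shows that the 66 contains no attrition margin.

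**Step 2: power of the same test on complete cases**

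The loss rates are assumptions. Loss means the share of children missing at least one of T2, T4 and T5.

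| Assumed loss | Complete cases, 66 × (1 − loss) | λ | Power |
|---|---|---|---|
| 0% | 66 | 9.90 | .802 |
| 5% | 63 (62.7) | 9.45 | .781 |
| 10% | 59 (59.4) | 8.85 | .752 |
| 15% | 56 (56.1) | 8.40 | .727 |
| 20% | 53 (52.8) | 7.95 | .701 |

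**Step 3: what a margin would have required**

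To finish with 66 complete children, allocate 66 / (1 − loss), rounded up: 70 at 5%, 74 at 10%, 78 at 15% and 83 at 20%.

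**The case against.** **No dropout rate is given.** A reader might infer that the trial will fail to reach .80. The documents do not support that: with no loss power is .80, and at 5% loss it is .78. This part of the objection stands, and the shortfall is conditional.

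**Discarding incomplete children is not a stated rule.** It is a property of the classical method. Rules for missing data, the analysis set and retention may sit in a full protocol or analysis plan that is not shown, and their absence from an article is no fault. Nothing says that children who stop training will not be assessed at T4 and T5. This also stands. What remains is that the article itself fixes the number, its derivation and the method.

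**The ANCOVA route would keep a child who missed only T5.** True if T4 is its dependent variable. However, that route is triggered by a significant baseline difference, not by missing data, so it does not protect against loss.

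**The Discussion remark on dropout.** The article says "particularly children with ADHD have problems taking part in traditional sports programmes and not dropping out of these". A reader might take this as the authors' forecast of dropout here. It concerns traditional programmes and is part of the argument for trying something else; elsewhere the article expects gaming to help motivation. The right to withdraw is likewise a standard consent term, not a forecast. I rest nothing on either.

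**The effect may be larger.** The aims section expects small to moderate primary effects. At f = .12, 53 complete cases would still give .856. That is correct, but the trial was sized on a small effect, and the stated .80 refers to that.

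**Is the randomised comparison lost?** A reader might go that far. It does not follow. Complete-case analysis exposes the comparison to bias if missingness relates to arm and outcome; it does not by itself remove the randomisation.

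**Conclusion.** The point holds in conditional form. The number allocated equals the minimum for complete data, so the stated power has no allowance for loss. If the named ANOVA is run in its classical form, power for the three-measurement interaction falls from .80 to about .78, .75, .73 and .70 at assumed losses of 5%, 10%, 15% and 20%. Bias is possible if missingness relates to arm and outcome, but the documents give no means of sizing it.

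The figures rest on f = .10, ε = 1 and the assumed loss rates. The first two are well supported because together they return exactly 66; the loss rates are illustrative. The point deserves correction because a method that keeps the observed scores is readily available, not because failure has been shown.

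**What to change.** 1. In Data analysis, replace the repeated-measures ANOVA with a linear mixed model for repeated measures on all randomised children as allocated. Include group, visit and group-by-visit, adjust for the T2 score, and use an unstructured covariance across T4 and T5. Every observed T4 and T5 score then contributes, so a child who misses T5 still supplies T4. The model is valid if missingness depends only on observed data.

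2. In Participants, state that the .80 applies to the three-measurement interaction test and only if essentially all 66 children complete. Give .70 to .78 as the complete-case ANOVA power under assumed losses of 20% down to 5%. Do not present these values as the power of the mixed model or of a T4 contrast: those are different tests, and their power depends on how the effect develops between T4 and T5.

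**Cost.** Slightly more analysis work in standard software, and a slightly less favourable power statement. No extra recruitment is needed.
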